### Concealment mechanism {16b}

The allocation is concealed in opaque, sealed envelopes.

### Implementation {16c}

The doctor examining the patient enrolls the participant. Together with the research nurse, an envelope (in consecutive order) is drawn. Either the doctor or the nurse informs the participant of the allocation.

## Assignment of interventions: blinding

### Who will be blinded {17a}

Interventions are not blinded, neither to healthcare personnel nor the patient.

### Procedure for unblinding if needed {17b}

Not applicable, as the interventions are not blinded.

## Data collection and management

### Plans for assessment and collection of outcomes {18a}

Data will be collected at inclusion and during follow-up visits at 0–4 days, 3 weeks, 3, 6, and 12 months from injury (Table 1). At the time of inclusion, written informed consent will be obtained, and the inclusion protocol, including inclusion and exclusion criteria as well as demographic data (age, gender, smoking habits, handedness, occupation, comorbidities, injury mechanism, level of injury, injured hand, injured finger, injured nerve, distance from injury to fingertip, and time from injury to treatment), will be completed. After consenting to participate, randomization will be carried out, and PROMs (Quick-DASH, HADS, HQ-8 (before operation), PCS) will be filled out. Sensory relearning is offered 0–4 days after injury. At 3 weeks, the cast and sutures will be removed by a nurse before seeing the occupational therapist. At follow-up visits, the investigating occupational therapist uses the follow-up study protocol for assessments (S2PD, AROM, SWM, Mini Sollerman test, Temperature sensation, Sharp/Dull, Grip strength + VAS, Pinch grip + VAS) and PROMs (Quick-DSAH, HQ-8 after operation/treatment, DN4), to make sure that all measurements and forms are completed.

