### Intervention description {11a}

At first examination, eligibility criteria, demographics, and information regarding the injury and its extent (perceived gender, date of birth, smoking, dominant hand, injured hand, profession, date of injury, injury mechanism, injured finger, injured nerve (ulnar/radial), level of injury (proximal or middle phalanx)) will be registered. Clinical examination will include sensory evaluation with S2PD of both the injured and the contralateral finger, as well as measurement of the distance between the injury and the fingertip in millimeters. Participants will be randomized to either nerve repair and cast or cast immobilization alone.

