### Control group

Cast immobilization will be maintained for 3 weeks. The cast will be administered by a nurse on the day of allocation.

In both groups, immobilization will consist of a cast over the wrist, stabilizing the metacarpophalangeal (MCP) joints in flexion and the proximal interphalangeal (PIP) joints in extension. Fingertips are left exposed to allow for sensory relearning exercises. Adjacent uninjured fingers will be included in the cast depending on the injury site and surgeon’s preference.

The follow-up protocols will be identical for both groups. All participants will be referred to an occupational therapist specialized in nerve rehabilitation to initiate early sensory relearning within 0–4 days following inclusion in the study. At 3 weeks, the cast and sutures will be removed. At this time, the occupational therapist will evaluate finger movement, sensation, strength, and overall hand function using standardized assessments, including active range of motion (AROM), S2PD, Semmes–Weinstein monofilament test (SWM), temperature and sharp/dull discrimination, the Mini Sollerman test, grip strength using the Jamar dynamometer, and Key pinch strength using the Pinch gauge. Follow-up evaluations will be conducted at 3, 6, and 12 months after inclusion (Table 1).

**Table 1 Tab1:** COPS trial participant timeline

	Study period							
	Enrolment	Allocation	Post allocation/surgery					Close out
**Timepoint**	*-t*_*1*_	0	0–4 days	3 weeks	3 months	6 months	12 months	> 12 months

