## Statistical methods

### Statistical methods for primary and secondary outcomes {20a}

Primary outcome is a dichotomous outcome that will be presented as proportions of patients obtaining return of 2PD < 10 mm 1 year after injury, presented with 95% confidence interval, and proportions between groups will be compared with Chi^2^ analysis.

All numerical values will be tested for normality by Shapiro–Wilk’s test.

We assume normality/parametric data for age, AROM, and grip strength. Results are presented as numerical values on an interval scale. Central tendencies of data will be described as means with their corresponding standard deviation, and comparisons between groups will be performed with Student’s *t*-test or repeated measures ANOVA.

Categorical data will be presented as proportions and compared by Chi^2^ analysis, unless Fisher’s exact test is demanded due to expected small numbers. Ordinal data will be presented as medians and interquartile range (IQR), and Mann–Whitney *U*-tests or Wilcoxon’s test used for comparisons between groups.

We assume a skewed distribution for time to injury, sick leave, and PROMs, which will be presented as medians with IQRs and compared by Mann–Whitney *U*-tests or Wilcoxon’s test.

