## Discussion

This randomized controlled trial addresses an important and clinically relevant uncertainty regarding the optimal management of digital nerve injuries by evaluating whether surgical treatment with epineural sutures provides superior outcomes compared with non-operative treatment in a plaster cast. In addressing this clinically relevant uncertainty, the trial limitations should be considered. Despite the randomized controlled design, potential sources of bias remain, including selection bias during recruitment and attrition bias due to loss to follow-up. The current gold standard of treatment for digital nerve injuries is surgical treatment with neuroraphy. Patients willing to undergo randomization between treatment strategies that deviate from established standard-of-care pathways may not be fully representative of the broader patient population, potentially limiting the external validity of the trial. The study is not blinded. Therefore, the risk of outcome assessment bias will also be present. Participants who know they received the “recommended treatment” may be more likely to report improvement than those who did not. The occupational therapists performing the follow up measures, may unconsciously rate outcomes differently depending on the participant’s treatment group. These limitations should be considered alongside several important strengths. The randomized controlled design provides a robust framework for evaluating the comparative effectiveness of the interventions. The inclusion and exclusion criteria were carefully selected to define a clinically relevant study population, while the primary outcome was defined a priori and selected based on its widespread use thus facilitating comparisons with previous studies. Furthermore, the sample size calculation was based on prespecified and clinically justified assumptions to ensure adequate statistical power. Finally, prospective publication of this study protocol enhances transparency and methodological rigor by documenting the prespecified study design, outcomes, and analytical approach, thereby reducing the risk of selective outcome reporting and facilitating assessment of adherence to the original study plan. 

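### The four baseline questionnaires are filled out after randomization in an open-label trial, so their inclusion values can reflect knowledge of the assigned arm

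*Protocol article*

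**What the plan says.** Under Plans for assessment and collection of outcomes {18a}, the order at inclusion is consent, randomization, questionnaires: "After consenting to participate, randomization will be carried out, and PROMs (Quick-DASH, HADS, HQ-8 (before operation), PCS) will be filled out". Table 1 agrees to the extent that it puts these four instruments in the allocation column (time 0) with randomization, while screening and consent are in the enrolment column.

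Implementation {16c} describes the draw and the disclosure: "Together with the research nurse, an envelope (in consecutive order) is drawn", and then "Either the doctor or the nurse informs the participant of the allocation". Who will be blinded {17a} adds: "Interventions are not blinded, neither to healthcare personnel nor the patient". For the control group, "The cast will be administered by a nurse on the day of allocation".

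Intervention description {11a} lists what is done at the first examination before it mentions randomization. That list has eligibility, demographics, injury details, the injury-to-fingertip distance and S2PD ("Clinical examination will include sensory evaluation with S2PD of both the injured and the contralateral finger"), but no questionnaire.

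The planned PROM analysis, in section {20a}, is descriptive plus rank tests: "We assume a skewed distribution for time to injury, sick leave, and PROMs, which will be presented as medians with IQRs".

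**The concern.** A baseline measurement is useful because randomization cannot have influenced it. Once an unblinded participant has been told the arm, a self-reported score no longer has that property. The article calls surgical repair the gold standard, so hearing that one has drawn operation or cast could move ratings of anxiety, pain-related helplessness or perceived disability. A physical route also exists. The cast is applied on the day of allocation and its order relative to the forms is not fixed, so some control participants might rate hand disability and stiffness with a cast on, whereas the HQ-8 form in the surgery arm is by its label pre-operative.

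Three uses of the data are at stake:

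- **Baseline table.** A between-arm difference in these scores could not be attributed to chance rather than to disclosure.
- **HADS and PCS.** Their sections justify them as possible contributors to post-surgical pain. Each is collected once only, so no clean value exists to fall back on.
- **Quick-DASH and HQ-8.** Both are repeated at 3, 6 and 12 months, so a reader will be inclined to compute change from inclusion or to adjust for it.

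**Working it through.** The plan gives no figure to reproduce, because the point concerns the order of procedures. The check has two parts.

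**1. Order of events, by section**

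| Step | Where stated | Relative to randomization |
|---|---|---|
| Consent | {18a}; Table 1, enrolment column | Before |
| S2PD (both fingers), injury-to-fingertip distance | {11a}, listed before randomization is mentioned; {18a} also lists distance in the inclusion protocol | Before |
| Envelope drawn, participant told | {16c} | Is the randomization |
| Quick-DASH, HADS, HQ-8 (pre-operative form), PCS | {18a}; Table 1, allocation column | After, as written |
| Cast in control group | Control group section | Same day; order relative to the forms not given |

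No section says that the forms are finished before the envelope is opened or before the participant is told. The Table 1 column alone would be weak evidence: it also holds the inclusion protocol and S2PD, which the text describes before randomization. The finding therefore rests mainly on the sentence in {18a}, read with {16c} and {17a}.

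**2. Which analyses could be biased**

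Let *d* be the between-arm shift in a baseline PROM caused by knowing the allocation, in SD units, and *ρ* the correlation between baseline and follow-up. Assume equal SDs and a shift that does not itself carry over to follow-up. The bias in the estimated arm difference is then:

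- follow-up value alone: 0
- change from baseline: −*d*
- baseline-adjusted (ANCOVA): −*ρd*

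The document gives neither *d* nor *ρ*. The values below are assumptions for illustration:

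| *d* (SD) | *ρ* | Follow-up only | Change score | Baseline-adjusted |
|---|---|---|---|---|
| 0.1 | 0.3 | 0 | −0.1 | −0.1 × 0.3 = −0.03 |
| 0.1 | 0.7 | 0 | −0.1 | −0.1 × 0.7 = −0.07 |
| 0.2 | 0.5 | 0 | −0.2 | −0.2 × 0.5 = −0.10 |
| 0.3 | 0.3 | 0 | −0.3 | −0.3 × 0.3 = −0.09 |
| 0.3 | 0.7 | 0 | −0.3 | −0.3 × 0.7 = −0.21 |

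The sign depends on which arm is shifted and in which direction, and the document does not settle that.

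Next, the stated analyses. Section {20a} gives between-group rank tests for PROMs and names no change score or baseline adjustment for them. The adjusted model for the primary outcome in {20b} lists age, gender, smoking, handedness and injury characteristics, but no PROM. The list is open-ended, however. DN4, which drives the interim rule, is first collected at 3 weeks and so has no baseline to contaminate. As stated, then, the plan's follow-up comparisons fall in the zero-bias column.

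**The case against.** The strongest reply is that no stated analysis is distorted. The primary endpoint is S2PD at 12 months, PROMs are compared between groups by rank tests, and HADS and PCS enter no listed model. This stands, and it limits the point to the baseline table, the interpretation of HADS and PCS, and analyses that someone might add.

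A reader might go further and infer from Table 1 that S2PD and the distance measurement are also taken after allocation. The text does not support this: {11a} describes both before randomization. Only the table column is out of line.

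A reader might also speak of a treatment effect at baseline. That is too strong. In the surgery arm the questionnaires precede the operation, so only knowledge of the allocation can act. In the cast arm an effect of the cast is possible but not established. Nor does the Discussion settle the matter. Its remark that participants who know they had the recommended treatment "may be more likely to report improvement than those who did not" concerns reporting at outcome assessment. It shows that the authors accept the general mechanism, not that inclusion scores are shifted. The PCS section also describes catastrophizing as possibly a personality factor, which would make it less responsive to a single piece of news.

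Finally, the order is joined in {18a} by a bare 'and', so forms might in practice be completed before disclosure. That is possible, but the natural reading is the sequence as written, and no other section protects the baseline.

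**Conclusion.** The point holds in limited form. As written, Quick-DASH, HQ-8, HADS and PCS at inclusion are post-randomization measurements in participants who know their arm, and they should not be treated as clean baselines. This matters most for HADS and PCS, which have no other time point.

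It would be wrong to conclude that the primary result or the planned follow-up PROM comparisons are biased by this ordering. Under the article's stated analyses that bias is zero.

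For a change-score or baseline-adjusted PROM analysis, the size cannot be estimated from the document. If the shift were 0.1 to 0.3 SD and the correlation 0.3 to 0.7, the bias would be 0.10 to 0.30 SD for change scores and 0.03 to 0.21 SD after adjustment, but those inputs are assumptions. The conclusion also assumes that practice follows the order in {18a}.

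**What to change.** Amend {18a} to state that the four questionnaires are completed after consent and before the envelope is opened, at the same visit, and move their rows in Table 1 accordingly. S2PD and distance need no reordering. Their Table 1 entries only need to be aligned with {11a}.

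For participants already enrolled, label the inclusion PROMs as post-allocation in the baseline table, do not use them for change scores or adjustment, and rest PROM comparisons on follow-up values. Where the actual order for a participant is known, record it.

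The direct cost is a short protocol edit and a different order of paper forms. It does not touch treatment, sample size or the primary analysis. The real drawback is that recruitment began in August 2022, so the trial will hold both pre- and post-allocation baselines, and the report must say which is which. With inclusion expected to run to the end of 2030, the change would still benefit everyone recruited from now on.

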### Plans to promote participant retention and complete follow-up {18b}

Participants who fail to complete questionnaires or to attend follow-up visits will be contacted by phone and/or mail by study group members.

### Data management {19}

Protocols and PROMs are completed on paper and stored in the participant’s file, which is kept in a locked archive space only accessible to the study group.

Data is entered from paper protocols into a computerized statistical program. Data accuracy will be verified through continuous review to check for input errors.

### Confidentiality {27}

Information about participants may be shared within the research team, research nurse, and occupational therapists from the date of inclusion through to 1-year follow-up. Follow-up protocols and PROMs on paper are stored in a locked archive space at Södersjukhuset hospital. At the end of the follow-up period, data is transferred from paper protocols into a computerized statistical program in pseudonymized form. The file is stored in a password-protected domain. The key linking the sequential number to the personal identification number is stored for 10 years in a locked archive space at Södersjukhuset.

### Plans for collection, laboratory evaluation and storage of biological specimens for genetic or molecular analysis in this trial/future use {33}

Not applicable, as no laboratory or biological specimens will be collected in this study.

## Statistical methods

### Statistical methods for primary and secondary outcomes {20a}

Primary outcome is a dichotomous outcome that will be presented as proportions of patients obtaining return of 2PD < 10 mm 1 year after injury, presented with 95% confidence interval, and proportions between groups will be compared with Chi^2^ analysis.

All numerical values will be tested for normality by Shapiro–Wilk’s test.

We assume normality/parametric data for age, AROM, and grip strength. Results are presented as numerical values on an interval scale. Central tendencies of data will be described as means with their corresponding standard deviation, and comparisons between groups will be performed with Student’s *t*-test or repeated measures ANOVA.

Categorical data will be presented as proportions and compared by Chi^2^ analysis, unless Fisher’s exact test is demanded due to expected small numbers. Ordinal data will be presented as medians and interquartile range (IQR), and Mann–Whitney *U*-tests or Wilcoxon’s test used for comparisons between groups.

We assume a skewed distribution for time to injury, sick leave, and PROMs, which will be presented as medians with IQRs and compared by Mann–Whitney *U*-tests or Wilcoxon’s test.

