## Trial design {8}

This is a single-center, unblinded, superiority, randomized controlled trial. The study includes patients with isolated digital nerve injuries, defined as a single digital nerve laceration without concomitant injury to flexor or extensor tendons, or to adjacent digital nerves. Patients will be randomized in a 1:1 ratio, without stratification, to either surgical nerve repair and cast, or immobilization only.

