### Eligibility criteria {10}

Patients presenting with a suspected digital nerve injury will be referred to and examined at the Department of Hand Surgery at Södersjukhuset by the on-call surgeon, according to standard procedure. The eligibility criteria for this study will be assessed during the examination.

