### Participant timeline {13}

#### Sample size {14}

This study was designed as a prospective superiority trial, aiming to determine whether one treatment strategy resulted in a superior sensory recovery outcome compared to the other. The primary endpoint was the proportion of participants achieving recovery of sensibility, defined as S2PD ≤ 10 mm, measured at the 1-year follow-up.

A power calculation was performed based on the assumption of a 20% clinically meaningful difference between groups. Using a two-sided significance level of *p* < 0.05 and a statistical power of 80%, the required sample size was calculated to be 150 patients. This calculation was based on an expected outcome proportion derived from a previously published study [38]. To account for an anticipated dropout rate of 10%, the total sample size was adjusted to 166 participants.

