### Recruitment {15}

Inclusion started on the 29th of August 2022. The closing date is anticipated to 31 st of December 2030. All patients seeking care in the Södersjukhuset hospital due to a suspected digital nerve injury are screened for inclusion and exclusion criteria, and all eligible patients are invited to participate. All eligible individuals who decline participation will have their reason for non-participation documented. Additionally, for participants who withdraw from the study or follow-up, their reason for withdrawal will be recorded, if possible.

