### Methods for additional analyses (e.g. subgroup analyses) {20b}

The primary outcome will be analyzed with mixed models effects, taking possible confounders into account, such as age (years), gender (female/male), smoking (yes/no), handedness (left/right), injury mechanism, level of injury (proximal/middle phalanx), distance from injury to fingertip (mm), time from injury to operation/immobilization (days). No other additional or subgroup analyses are planned.

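### The primary endpoint is named return of S2PD but scored as a fixed 12-month level with no baseline condition, and no stated analysis uses the inclusion S2PD

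*Protocol article*

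**What the plan says.** All references are to the Protocol article.

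- **Endpoint.** Statistical methods {20a} compares "proportions of patients obtaining return of 2PD < 10 mm 1 year after injury" by a chi-squared test. Sample size {14} speaks of recovery of sensibility, "defined as S2PD ≤ 10 mm, measured at the 1-year follow-up". Both are absolute 12-month thresholds, and they differ on whether exactly 10 mm counts.
- **Entry.** Trial design {8} has the injury "defined as a single digital nerve laceration without concomitant injury to flexor or extensor tendons". It does not say whether the laceration must be complete. The inclusion criteria ask for a sharp, isolated single digital nerve injury, and neither they nor the exclusion criteria mention sensation. Under Eligibility criteria {10}, "Patients presenting with a suspected digital nerve injury will be referred to and examined" by the on-call surgeon. Recruitment {15} says that all patients attending "due to a suspected digital nerve injury are screened for inclusion and exclusion criteria".
- **Baseline value.** Intervention description {11a} says "Clinical examination will include sensory evaluation with S2PD of both the injured and the contralateral finger". Table 1 lists S2PD in the allocation column.
- **Control arm.** "The cast will be administered by a nurse on the day of allocation"; no exploration of the nerve is described.
- **Adjusted analysis.** The covariates in {20b} run from age to "distance from injury to fingertip (mm), time from injury to operation/immobilization (days"). Inclusion S2PD is not named. The section ends by saying that no further additional or subgroup analyses are planned.

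**The concern.** Return and recovery describe something lost and then regained. The scored quantity is a level at one time point. A participant who reads 8 mm at inclusion and 8 mm at 12 months is counted as having regained sensation, although nothing changed.

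Such participants succeed whichever treatment they receive. They raise both proportions and pull the difference towards zero, so a real advantage of either strategy becomes harder to detect. The trial asks whether suturing gives better sensory recovery than a cast. If it ends without a significant difference, the reader will want to know whether the strategies perform alike in people who lost discrimination, or whether the sample held people with little to regain. The value that would answer this is already collected, but no stated analysis uses it.

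**Working it through.** **Inputs from the documents.** Two-sided 5% level, 80% power, a 20% difference (read as 20 percentage points), 150 evaluable patients and 166 in total (Sample size {14}); 1:1 allocation (Trial design {8}), hence 75 per arm.

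**Assumed inputs.** The expected proportion is not stated, and neither is f, the share already under the cut-off at inclusion.

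**Step 1: the plan's own figure.** The 150 cannot be reproduced directly without the base proportion. Scanning all pairs 20 points apart with the pooled-variance formula and no continuity correction, 64% v 84% and 16% v 36% each give exactly 75 per arm. A mid-range pair does not fit: 40% v 60% needs 194 in total. Both fitting pairs are carried forward.

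**Step 2: dilution.** If a share f is under the cut-off at inclusion and stays there in both arms, each arm's success proportion p becomes

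p′ = f + (1−f)p,

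and the difference becomes (1−f)d.

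**Step 3: power with n = 75 per arm.**

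Power = Φ{[d′ − 1.96·√(2p̄(1−p̄)/n)] / √([p₁′(1−p₁′) + p₂′(1−p₂′)]/n)}, with d′ = p₂′ − p₁′ and p̄ the mean of p₁′ and p₂′.

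Worked example, 64% v 84% with f = 10%:
- p₁′ = 0.10 + 0.90×0.64 = 0.676
- p₂′ = 0.10 + 0.90×0.84 = 0.856
- d′ = 0.180, p̄ = 0.766
- Null standard error = √(2×0.766×0.234/75) = 0.0691
- Alternative standard error = √((0.2190 + 0.1233)/75) = 0.0676
- z = (0.180 − 1.96×0.0691)/0.0676 = 0.66, so power is 74.5%

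| f (assumed) | Difference, points | Power, 64% v 84% | Power, 16% v 36% |
|---|---|---|---|
| 0 | 20.0 | 80.4% | 80.4% |
| 5% | 19.0 | 77.5% | 72.6% |
| 10% | 18.0 | 74.5% | 65.0% |
| 20% | 16.0 | 67.8% | 51.4% |

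The loss is larger for the low pair because adding certain successes moves its proportions towards 50%, where the variance is greatest.

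**Step 4: the restricted comparison.** Leaving out those under the cut-off at inclusion restores d = 20 points with 75(1−f) per arm. Power is then 78.3% at f = 5%, 76.0% at 10% and 71.0% at 20%. The figures are the same for both pairs, because 16% v 36% mirrors 64% v 84%. In each case this is above the pooled figure, by 0.8, 1.5 and 3.2 points for the high pair, but it does not return to 80%.

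**The case against.** **The share f is unsupported and probably small.** This stands. Trial design {8} speaks of a laceration, and a surgeon in a hand surgery department judges eligibility at an examination that itself includes S2PD. If nobody with intact discrimination is enrolled, there is no dilution. If the cited planning study had a similar mix, part of the dilution may already be in the assumed 20%. The power figures are scenarios, not estimates.

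**The primary comparison is valid as it is.** This also stands. Sample size {14} defines recovery as a level, randomisation balances baseline in expectation, and the trial compares strategies in patients diagnosed before any exploration. A reader might infer that the intention-to-treat result is biased between arms. The documents do not support that; the issue is sensitivity and interpretation.

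**The covariate list is open.** It is introduced by *such as*, so inclusion S2PD is unnamed rather than ruled out. That is correct, and the point is limited to its not being named.

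**A sensitivity analysis belongs in the statistical analysis plan.** Ordinarily yes. Here {20b} states that no other additional analyses are planned, and {31c} calls the document the complete protocol. The article therefore closes the list rather than leaving it to another document.

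**Selecting on baseline S2PD is safe only if it is measured before allocation.** This stands. The order of sentences in {11a} implies that it is, but Table 1 puts it in the allocation column, {18a} does not list it among the inclusion data, and the trial is unblinded. The documents do not support a claim that the selection cannot bias the arms until the timing is confirmed.

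**An undetected partial or absent laceration in the cast arm is a separate matter.** True. A baseline S2PD condition does not verify the nerve.

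**Conclusion.** The endpoint's name and its scoring do not match. Nothing in eligibility or the stated analyses makes up for this, although the needed measurement exists. Participants under the cut-off at entry who stay there shrink a difference d to (1−f)d.

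For assumed f of 5% to 20%, power falls from 80.4% to between 77.5% and 67.8% (64% v 84%) or between 72.6% and 51.4% (16% v 36%). This rests on an undocumented f, on an inferred base pair, and on these participants remaining successes in both arms. At f = 0 there is no loss.

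A reader might infer that the trial is materially underpowered, or that its primary population or eligibility criteria must change. The documents support neither. Without f no loss can be asserted, and Protocol amendments {25} already reports a low inclusion rate, so narrower entry would have a real price. What they do support is a low-cost supporting analysis, without which a null result could not be fully interpreted.

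**What to change.** 1. Reconcile the cut-off first: ≤ 10 mm in Sample size {14} and < 10 mm in Statistical methods {20a} cannot both define the endpoint or the baseline rule.
2. Confirm, and state, that S2PD of the injured finger is recorded before the randomisation envelope is opened.
3. Keep the primary analysis by intention to treat in all randomised participants.
4. In {20b}, add a prespecified sensitivity analysis of the primary outcome by randomised arm, restricted to participants whose inclusion S2PD on the injured side is above the agreed cut-off or not measurable. Amend the sentence that rules out further analyses.
5. Name inclusion S2PD as a covariate in the adjusted model, and say how a non-measurable value is coded.
6. Report, per arm, the number under the cut-off at inclusion. This gives f directly and shows whether the concern matters.

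The cost is a few sentences, with no new data collection. The downside is a somewhat smaller supporting analysis, at 75(1−f) per arm under the planned numbers. Changing the primary population or the eligibility criteria is optional and is not needed to meet the point.
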